### Objectives

The primary purpose of the present trial is to investigate the effectiveness of a mobile application in improving hospitalized Corona patients' psychological parameters such as depression, anxiety, and stress. The trial will also assess any change to respiratory/non-respiratory symptoms in the control and intervention groups.

### Control Group

Participants in the usual care group will receive standard care as provided by their physicians at the time of hospitalization. After discharge, they will be recommended to use the general counseling facilities available to the public as soon as required.

### Intervention Group

All patients participating in the intervention group will have to install a user-friendly mobile-based psychological counseling and health status monitoring application named “SarveDigital” on their mobile phones. They will also receive usual care the same as the control group.

Participants in the intervention group will be provided with oral and printed instructions for accessing and logging into the application. To access the application, it is necessary to fill in a personal form. Once this is adequately completed, the app services can be accessed.

Participants will be advised to have full access to the program until 2 weeks after discharge, and will be encouraged to use the program regularly. They will be recommended to use the educational content of the application and ask their questions from a physician via the application.

### Intervention

#### Need Analysis

In designing the application for COVID-19 patients, the first step was to extensively review the related literature on the pre-existing applications in terms of effectiveness, appropriateness to the target group, specific features, and probable discussions in design. Then, in several meetings with internal specialists, psychologists, sports consultants, and medical informaticians (no. of experts = 5), the scientific aspects of the topic, patients' needs during hospitalization and after discharge and the necessity of offering complementary solutions were analyzed. Consequently, according to the present findings, experts' comments and patients' cultural and local tendencies, the main features of the application were specified for the design.

#### Design Process

In order to design the technical features of the application and apply the maximum capabilities of the mobile application production domain, a team of experts was consulted. The original idea of the application was discussed in meetings shared between the clinical and technical teams. The ambiguities were solved and the technical aspects were discussed.

Eventually, considering the fact that the main goal of developing the application is establishing interactive communication between patients and healthcare providers, a mobile application was designed to support patients physically and psychologically.

During the design procedure, a formative evaluation was used and the feedback received from the experts and sample patients helped to remove the existing defects. The major changes to the application were: change in content, content categorization, larger font size, and change from a native app approach (Android-based application) to a web-based approach (web-based application) due to its compatibility with all smartphones regardless of the operating system. It will be possible to use the application for more patients.

#### Application Features

The mobile application has been designed with a simple, intuitive user interface.

The application consists of 4 main parts (Figure 2):

**Education:** This part consists of a broad range of educational content during hospitalization and after discharge including psychological, general exercise, medical and health videos and texts about COVID-19 patients. The educational material required for COVID-19 patients will be provided using valid educational resources and experts' consensus.To improve the content in later versions of the software, at the end of each educational medium, the patient will be asked to rate the content and help us increase the quality of services.**Contacting Care Providers:** This part serves the following functions:Support by other medical staff besides the attending physicians such as psychologists who cannot be physically present in the clinic for safety matters.Patient-physician communication via software in hours later than daily visits. Besides filling out an improvement checklist, the patient can write a text about personal queries and concerns.Physician's (or any other therapist's) feedback for patient. Upon seeing the patient's text, the therapist can send a text-based or audio message as the response (to relieve the patient).Contacting care providers will be disabled at the end of the study (2 weeks after discharge).**Symptoms Self-report:** SarveDigital will help COVID-19 patients record their symptoms and, thus, their physician will be able to monitor and control their condition from a distance. Patients will be asked to enter their health symptoms such as fever, sore throat, dry cough, difficulty breathing or the shortness of breath, and loss of taste or smell at least three times a week into the application. Each symptom will be rated on a 4-point scale (e.g., “no fever,” “mild fever,” “moderate fever,” and “high fever”).These data will automatically be sent to the physicians' portal so that the physician will be aware of the patient's health status. It should be noted that the attending physician and the psychologist assigned will be able to access physicians' portal via their mobile phone with a username and password. This will ensure the privacy and security of the patient's information and the relevant classified information (26).**Care Providers' Biography:** This part introduces the key information about the attending physician and psychologist who will communicate with the patient. The aim is to increase the trust the patient places in them to easily share concerns, queries and else.

**Figure 2 F2:**
[figure not shown]
Screenshot of **(A)** home page view, **(B)** education, and **(C)** symptoms self-report.

### Outcome Measures

#### Primary Outcomes

The primary outcome will be a change to the patient's depression anxiety stress scales-21 (DASS-21) score from baseline to 2 weeks after discharge from hospital. It will be measured at the baseline, upon discharge and 2 weeks afterward. It should be noted that baseline measurements will be collected as soon as the patient is admitted to the hospital. This will ensure that almost all patients are included under the same conditions.

#### Secondary Outcomes

Changes to the respiratory symptoms including the respiratory rate will be determined through physician assessment; oxygen saturation will be measured through pulse oximetry; lung involvement will be checked by imaging at the time of discharge.Changes to the non-respiratory symptoms including multi-organ failure will be determined through kidney and liver function tests; fever will be measured with a thermometer; secondary infection will be measured by physician assessment at the time of discharge.

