### Randomization

www.randomization.com will be used to create a randomization sequence. The sequence of the generated random number will be inserted into envelopes sealed by an independent researcher (SA), not participating in the main data collection phase or in the intervention. These envelopes will be opened only after the participants sign the informed consent and complete all baseline assessments (FK). Then, the eligible participants will be randomly divided into two groups, a usual care group and an intervention group, which uses the application.

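### The secondary outcomes are called changes, but discharge is the only time named for them, and the article does not say whether the admission baseline includes them

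*Protocol article*

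**What the plan says.** The Objectives section of the protocol article sets the task: "The trial will also assess any change to respiratory/non-respiratory symptoms in the control and intervention groups". The Secondary Outcomes section uses the same idea for both groups of measures: "Changes to the respiratory symptoms including the respiratory rate will be determined through physician assessment", and "Changes to the non-respiratory symptoms including multi-organ failure will be determined through kidney and liver function tests".

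The only time in that section is discharge. It is attached to two items: "lung involvement will be checked by imaging at the time of discharge", and "secondary infection will be measured by physician assessment at the time of discharge". Respiratory rate, oxygen saturation, kidney and liver tests and temperature stand in clauses with no time of their own. The Data Collection Instruments section returns to these outcomes and lists the instruments, again without times.

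The primary outcome, the DASS-21, has a full schedule: "It will be measured at the baseline, upon discharge and 2 weeks afterward". Two other sentences refer to baseline data without listing them. Primary Outcomes says that "baseline measurements will be collected as soon as the patient is admitted to the hospital", and Randomization says: "These envelopes will be opened only after the participants sign the informed consent and complete all baseline assessments".

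For quantitative variables, Statistical Analysis plans an independent-sample t-test or a Mann-Whitney test, and repeated-measures methods for continuous outcomes measured more than once. It mentions no adjustment for a baseline value.

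**The concern.** A change needs a start and an end. The definition prints an end and no start, directly below a primary outcome for which both are given. Two readings stay open: status at discharge, or difference from an unnamed earlier value. They lead to different analyses with different precision, and the Statistical Analysis section does not settle which is meant.

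Three things are at stake. If the admission values are not collected in a uniform way, change cannot be reported for each arm, as the objective asks. If they are collected but not used as a covariate, precision is given away. If the choice is left until the data are in, it can be made with the results in view, in a trial whose outcome assessor is not blinded (Blinding section).

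The intervention arm's symptom reports in the application cannot supply the missing start, because the control arm does not have the application.

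**Working it through.** **Step 1. Timing, item by item.**

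| Item | Called a change? | Time stated | Admission value stated? |
|---|---|---|---|
| DASS-21 | yes | baseline, discharge, 2 weeks later | yes |
| Respiratory rate | yes | none of its own | no |
| Oxygen saturation | yes | none of its own | no |
| Lung involvement | yes | discharge | no |
| Kidney and liver tests | yes | none of its own | no |
| Temperature | yes | none of its own | no |
| Secondary infection | yes | discharge | no |

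The general baseline sentences could cover the last six rows, but they neither include nor exclude them.

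**Step 2. The plan's own figure.** Sample Size gives 95 per group for an effect size of 0.41, alpha 0.05 and power 0.80. The normal approximation gives 94, and the t-based calculation gives 94.35, rounded up to 95. The figure reproduces. It concerns the DASS-21 and serves here only as the number per arm. The Abstract gives a different total (112), but the variance ratios in step 3 do not depend on the number of patients.

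**Step 3. Precision of the three possible analyses.** Assume equal variance at admission and discharge, and an admission-discharge correlation r. The article gives no r, so 0.3 to 0.6 is an assumption. Relative to the variance of the discharge value (set to 1):

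- unadjusted discharge value: 1
- simple change score: 2(1 − r)
- discharge value adjusted for admission (ANCOVA): 1 − r²

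| r | Discharge only | Change score | ANCOVA | Variance removed by ANCOVA |
|---|---|---|---|---|
| 0.3 | 1.00 | 2 × 0.7 = 1.40 | 1 − 0.09 = 0.91 | 9% |
| 0.6 | 1.00 | 2 × 0.4 = 0.80 | 1 − 0.36 = 0.64 | 36% |

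ANCOVA is the most precise at both ends of the range. At r = 0.3 the simple change score is worse than ignoring the baseline.

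The standard error scales with the square root of the variance: √0.91 = 0.95 and √0.64 = 0.80. The confidence interval for the arm difference therefore narrows by about 5% to 20%.

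**Step 4. Chance imbalance at admission.** With 95 per arm, the difference in mean admission values has standard deviation √(2/95) = 0.145 SD, so a 95% range of ±1.96 × 0.145 = ±0.284 SD. Only the fraction r carries over to the discharge comparison: 0.284 × 0.3 = 0.09 SD to 0.284 × 0.6 = 0.17 SD. The ordinary standard error of the unadjusted comparison already contains this. It is the same loss as in step 3 seen from another side, not an additional bias.

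**The case against.** The strongest reply is that the article does provide for baseline data. The admission sentence in Primary Outcomes is plural and not restricted to the DASS-21, Randomization requires every baseline assessment before the envelope is opened, and an outcome called a change ordinarily implies an earlier value. Statistical Analysis also covers differences and repeated measurements in general terms. A schedule of variables by visit commonly sits in the full protocol, which is not shown, and the study schematic is missing from the extracted text.

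This stands against one inference. A reader might conclude that no admission value will be taken and that change cannot be calculated. The documents do not support that. They leave the content of the baseline set open, and change would be impossible only if that set were the DASS-21 alone.

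A second tempting inference is that, without an admission value, differences in severity pass straight into the result, with ±0.28 SD set against the planned 0.41 (0.284/0.41 = 69%). That fails too. Randomisation keeps the discharge comparison valid, the carry-over is only 0.09 to 0.17 SD at the assumed correlations, and 0.41 comes from a study of stress, anxiety and depression, so it is no benchmark for oxygenation or lung findings. Entry severity is not wholly unaddressed either, since the exclusion criteria list transfer to intensive care and physical deterioration, although their timing is unclear.

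The reply does not dispose of the printed definition, which says change and names one time. Nor do the repeated-measures methods close the gap: with two time points, the group-by-time test of repeated-measures ANOVA is the test of the simple change score, the least precise of the three analyses at r = 0.3.

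**Conclusion.** The point holds in a limited form. The secondary outcomes are called changes, discharge is the only time named for them, and the article does not say whether the admission baseline contains these variables. A comparison of discharge values would be valid. For a continuous measure in all randomised patients, its expected arm difference equals that of the change score. It would nevertheless describe status at discharge, and change in each arm could not be reported from it.

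The size is a loss of precision: 9% to 36% of the outcome variance, or about 5% to 20% in interval width. This rests on an assumed correlation of 0.3 to 0.6 and equal variances at the two times. The primary outcome and the sample size are not affected. It is a minor point and a cheap improvement.

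**What to change.** In Secondary Outcomes, name for each continuous measure the admission value that serves as baseline, taken before the envelope is opened, wherever one is on record: respiratory rate, oxygen saturation, temperature, kidney and liver tests, and lung involvement if it is scored numerically. In Statistical Analysis, state that the arms are compared on the discharge value adjusted for that admission value (ANCOVA), in place of an unadjusted discharge value or a simple change score.

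Reword any item without an admission value as status at discharge. Reword secondary infection as occurrence by discharge, since change has no natural starting value there.

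The cost is transcribing chart values onto the baseline form. No new tests are needed if these values are charted routinely at admission, which is an assumption that the article does not document. Some admission images or laboratory results will be missing, and the plan should say how those patients enter the adjusted analysis.

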#### Exclusion Criteria

unwillingness to continue with researchtransference to the wards where it is not possible to use a mobile phone, such as the intensive care unitdeterioration of the patient's physical condition.

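### Exclusion for intensive-care transfer or deterioration, if applied after randomisation, takes the patients who worsen out of the secondary-outcome comparison and contradicts the stated intention to treat

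*Protocol article*

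**What the plan says.** The Objectives section of the protocol article makes clinical course a between-group comparison: "The trial will also assess any change to respiratory/non-respiratory symptoms in the control and intervention groups". Study Design and Setting likewise asks whether the app leads to a better outcome in these patients.

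The Secondary Outcomes section gives the measures in two sentences:
- Respiratory: respiratory rate by physician assessment, "oxygen saturation will be measured through pulse oximetry", and "lung involvement will be checked by imaging at the time of discharge".
- Non-respiratory: changes to "non-respiratory symptoms including multi-organ failure will be determined through kidney and liver function tests", "fever will be measured with a thermometer", and "secondary infection will be measured by physician assessment at the time of discharge".

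The Exclusion Criteria list three items: unwillingness to continue, transfer "to the wards where it is not possible to use a mobile phone, such as the intensive care" unit, and deterioration of the patient's physical condition. The Statistical Analysis section states that the analysis is by intention to treat. Nothing says whether outcomes are still collected once a patient meets an exclusion criterion.

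**The concern.** Intensive-care transfer and physical deterioration are not neutral reasons for leaving a trial whose secondary outcomes include multi-organ failure, oxygen saturation and secondary infection. They are steps on the way to those outcomes. A patient developing organ failure would ordinarily meet the deterioration criterion before any reading at discharge, and a patient who dies is never discharged alive. If the criteria are applied to randomised patients, the comparison is conditioned on a post-randomisation event that the app might itself influence.

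The removal may also differ by arm. Under Application Features, intervention patients report symptoms at least three times a week to a portal that the attending physician can read. Under Blinding, the outcome assessor is unblinded and in constant contact with intervention patients. Deterioration may therefore be noticed, and acted on as an exclusion, more readily in one arm.

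What is at stake is the clinical half of the trial's question. A finding of no difference could reflect who was left to be measured, and an imbalance in exclusions could produce a difference where none exists.

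**Working it through.** **1. The plan's own figure.** The Sample Size section gives an effect size of 0.41, error probability 0.05, power 0.80 and 1:1 allocation; Statistical Analysis makes tests two-tailed. A two-sample t-test calculation gives 94.35, so 95 per arm and 190 in total, as stated. For 10% attrition, 95 × 1.10 = 104.5, rounded to the stated 105 (95 / 0.90 = 105.6 would give 106). The figure holds up, but it rests on stress, anxiety and depression, so nothing sizes the trial for the secondary outcomes. I use 105 per arm below. The abstract's total of 112 is a separate discrepancy.

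**2. The order of events.** Baseline is taken on admission (Primary Outcomes). Envelopes are opened after consent and all baseline assessments (Randomization). Ceasing to be willing, being transferred and deteriorating all describe a change after entry, so they fall mainly after allocation. Set beside the intention-to-treat statement, the two instructions cannot both be followed as written for such a patient.

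**3. What exclusion does to the contrast.** Let p be the true proportion who worsen and f the share of them excluded without follow-up, with nobody else excluded. Then

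observed proportion = p(1 − f) / (1 − pf), and patients lost per arm = 105 × p × f.

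The article gives no value for p or f, so all values here are assumptions. For 20% (control) against 10% (app) with f = 0.5: 0.10/0.90 = 11.1% against 0.05/0.95 = 5.3%. Power is for a two-sided 5% comparison of two proportions in the patients who remain.

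| True, control vs app | f | Lost, control / app | Observed | Difference (points) | Power |
|---|---|---|---|---|---|
| 20% vs 10% | 0 | 0 / 0 | 20.0% vs 10.0% | 10.0 | 53% |
| | 0.5 | 10.5 / 5.25 | 11.1% vs 5.3% | 5.8 | 32% |
| | 0.8 | 16.8 / 8.4 | 4.8% vs 2.2% | 2.6 | 16% |
| | 1 | 21 / 10.5 | 0 vs 0 | 0 | not defined |
| 30% vs 15% | 0 | 0 / 0 | 30.0% vs 15.0% | 15.0 | 74% |
| | 0.5 | 15.8 / 7.9 | 17.6% vs 8.1% | 9.5 | 50% |
| | 0.8 | 25.2 / 12.6 | 7.9% vs 3.4% | 4.5 | 26% |
| 15% vs 10% | 0 | 0 / 0 | 15.0% vs 10.0% | 5.0 | 19% |
| | 0.5 | 7.9 / 5.25 | 8.1% vs 5.3% | 2.8 | 12% |
| | 0.8 | 12.6 / 8.4 | 3.4% vs 2.2% | 1.2 | 8% |

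The absolute difference shrinks in every scenario and disappears only at f = 1. With the same f in both arms the ratio is roughly kept (11.1/5.3 = 2.1 against a true 2.0), so in that case the damage is mainly lost events and lost power.

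**4. If f differs by arm.** Take no true effect, 20% worsening in both arms, with f = 0.5 in control and f = 0.8 in the app arm. Observed: 0.10/0.90 = 11.1% in control and 0.04/0.84 = 4.8% in the app arm. That is an apparent benefit of 6.3 points created by the exclusions alone.

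**5. Timing.** In each of the two outcome sentences the discharge phrase comes at the end and belongs directly to the last item: lung imaging in one, secondary infection in the other. The clauses on oxygen saturation, fever and the kidney and liver tests carry no time of their own. Both sentences speak of changes, which implies an earlier value, but no assessment during the stay is stated. Even a change from admission to discharge misses an episode that began and resolved in between.

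**The case against.** The best defence has four parts.

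- The article does not say that all secondary outcomes are read only at discharge. That is correct: it is explicit for two items, and the reference to changes points to an earlier value. A visit schedule is also something a condensed article may leave to the full protocol, so unclear timing alone would be a weak point.
- The Exclusion Criteria do not say that follow-up stops or data are discarded, and intention to treat points the other way. This too is correct: loss of the excluded patients is an inference. But the two statements conflict, and a site following the exclusion list as written would remove these patients. That is a contradiction in the text, not merely absent detail.
- A reader might infer that the outcomes cannot capture worsening at all, or that the arms must look alike by construction. The article does not support that. It requires every worsened patient to be excluded and not followed (f = 1). Worsening not classed as deterioration, or still present at discharge, would be recorded, and imaging, respiratory rate and laboratory values can still differ between arms at discharge. No discharge criteria are given, so near-normal values at discharge cannot be presumed.
- These are secondary outcomes in a trial whose primary purpose is psychological. This limits the weight of the point but does not remove it, because the Objectives section commits to the comparison.

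**Conclusion.** The concern holds in a limited form. The Exclusion Criteria and the intention-to-treat statement contradict each other for patients who go to intensive care or deteriorate after randomisation, and these are the patients most likely to have the secondary outcomes. If the exclusions are applied after randomisation without further follow-up, much of the worsening is lost, possibly unequally by arm, and reading at discharge adds the loss of resolved episodes. A null secondary result could then not be taken as evidence of no clinical effect.

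The size is unknown, because the article gives no worsening rates. In the assumed scenarios, losing 50% to 80% of worsened patients takes a true difference of 10.0 points down to between 5.8 and 2.6, and power from 53% to between 32% and 16%. Power is modest even with nobody lost, since the trial was not sized for these outcomes. The conclusion rests on three assumptions: that the criteria act after randomisation, that excluded patients are not followed, and that the worsening rates are of the order shown. The first is the natural reading of the list; the article does not settle the other two. The point should be corrected but does not threaten the design of the primary comparison in the way shown here.

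**What to change.** Reconcile the Exclusion Criteria, Secondary Outcomes and Statistical Analysis sections:

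1. Separate criteria checked before randomisation from events after it. State that intensive-care transfer or deterioration after randomisation may bear on app use, which is for the investigators to settle, but is not a reason to leave follow-up or the analysis. For patients who withdraw, keep the data collected up to that point.
2. For all randomised patients, count multi-organ failure and secondary infection from randomisation to discharge or death, using the hospital chart. Report intensive-care transfer and death by arm alongside.
3. State the time points for oxygen saturation, respiratory rate and temperature, and compare the arms adjusted for the admission value. Describe discharge values as conditional on discharge alive.
4. Report by arm how many patients met each exclusion criterion after randomisation.

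Length of stay, or vital signs on one fixed day, could be added but are not needed. Filling a fixed-day measure with the last value before an earlier discharge would bring back readings at varying times.

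The cost is extra chart extraction at one hospital, with no added tests, provided that these data are routinely charted, which the article does not say. Recruitment was still incomplete when the article was written, so the change was feasible then.
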